**Methodology:** This cluster randomized control trial will be carried out in urban clusters (market place) treated as control and interventional sites A total of 556 consumers and at least 50 vendors of urban street cooked foods will be recruited. The study will involve the national food regulatory bodies, universities and ward and district experts responsible with food security and environmental safety. The intervention package to be applied to urban street consumers and vendors will include education on Type 2 diabetes and guidance on food intake using the food plate model. The package is composed of health education covering issues on risk factors, symptoms, prevention, complications of diabetes and nutritional values of foods. Education will be delivered through brochures, group education and if possible through mobile phone technology. Another component is a healthy plate model; a plate is composed of recommended potion of carbohydrate, protein, fruits and vegetables plus water/milk and safe cooking oil. The package will be evaluated to assess its effectiveness in reducing metabolic risk factors of type2 diabetes among urban street cooked food consumers. Determinants established during the intervention will be used in developing a model for predicting metabolic risk factors of type2 diabetes among urban street cooked food consumers by using Multivariate/Joint Bayesian modelling techniques. The study findings are envisaged to be used to inform appropriate interventions.

**Keywords:** Type2 diabetes metabolic risk factors, urban street cooked food vendors and consumers, type2 diabetes health education and food plate model.

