# 2.0 Materials and Methodology

2.1 Study area: This study will be conducted in Dar es Salaam region. Dar es Salaam is the largestcity in Tanzania with land area of 538km^2^. It has five municipalities namely Ilala, Kinondoni, Temeke, Ubungo and Kigamboni. The region/city contributes about 80% of all national economy thus attracting more immigrants from inside and outside of the country for economic investments. The city is the third fastest-growing in Africa and the ninth fastest-growing in the world. According to the national census report of 2012 the population of Dar es Salaam was 4.36 million (41)**.** The population of the region is expected to over double up to 10.76 million by 2030(42). This study will be conducted in three already randomly selected districts and six market places (two per district). The selected districts are Ilala, Kinondoni and Ubungo. The region was considered for this study because of previous researches which indicated that majority of low and income people in the area consume street foods served by street vendors(26,27). The studies also indicated that the nutrition value of the foods supplied by street food vendors is questionable as they normally serve smaller amount of fruits and rarely served fruits due to limited capital and low knowledge on nutrition values of foods (26,27)**.** Such eating behaviours expose the consumers at risk of getting type2 diabetes due to increased risk of metabolic risk factors. In Dar es Salaam it was also observed that costs and attitude were the factors associated with low consumption of fruits and vegetables among pupils and student (27). Another study conducted in Dar es Salaam among HIV positive people indicated that consuming junk foods led to increased body weight which was perceived a strategy for increasing CD4 counts (43)**.**

2.2 Study population: Urban regular eaters of street cooked food, vendors and key stakeholders. Key stakeholders will include health environmental officers, municipal nutritional officers and officers from the national food regulatory authorities.

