2.3 Study design: This study will be intervention (experimental) with two arms control and experimental clusters. This design is appropriate for this study since it will allow researchers to measure the effects of an intervention package (health education and plate model) by comparing the outcomes of the package in the experimental group versus control group which will receive a placebo (health education) after three months of follow up. Healthy plate will contain ¼ carbohydrate, ¼ protein, ¼ vegetables and ¼ fruits. Health education will focus on risk factors of type2 diabetes, prevention strategies and complications of the disease and nutritional values of foods. A proposed intervention package will be assigned to the clusters (market places) randomly but subjects in the intervention sites will not be blinded in order to get the desired outcomes and justify the efficacy of an experiment. Before intervention, baseline information including behavioural risk factors (physical inactivity, unhealthy diet, and smoking, harmful alcohol consumption), metabolic risks (raised blood pressure, triglyceride, blood glucose, low HDL and central obesity) and socio-economic and familial risks (sex, age, income, location, knowledge, family history of diabetes) will be collected from both arms.After intervention the same information collected at the baseline will also be collected at the end line.

2.4 Sample size: The sample was calculated by considering the following statistical parameters: level of significance (Z_1-α_), power of the test (Z_1-β_), population standard deviation (δ) and population variance (δ^2^).The baseline indicator for the mean waist hips ratio of µ_0_ =0.82 and a target of reducing the mean of waist circumference by 5% after an intervention i.e. from 0.82 to µ_a_=0.78. A design effects (DE) of 1.5 to clear variance between clusters was applied and none response rate of 20%. With the above statistical parameters then an actual sample size is 278 (**Table 1**). This sample size will be doubled to include both arms (intervention and control). Furthermore, at least 50 food vendors will be recruited and each food vendor will be asked to identify their regular clients who will be approached for the study.

Sample size (n) calculation formula (44).

**
[figure not shown]
**

Table 1 Estimated sample size per each risk factor indicator

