| **S/No** | **Parameter** | **µ_o_** | **Δ** | **δ^2^** | **Desired % change in mean after 3 months** | **µ_a_** | **DE** | **Non response (20%)** | **N** |
| --- | --- | --- | --- | --- | --- | --- | --- | --- | --- |
| 1 | BMI(Kg/m^2^) | 22.9 | 4.6 | 21.2 | 5 | 21.8 | 1.5 | 0.8 | 204 |
| 2 | TC(mmol/L) | 4.6 | 0.78 | 0.6 | 5 | 4.4 | 1.5 | 0.8 | 178 |
| 3 | TG(mmol/L)* | 1.7 | 1.1 | 1.2 | 12 | 1.5 | 1.5 | 0.8 | 353 |
| 4 | SBP (mmHg) | 129 | 21.3 | 453.7 | 5 | 122.2 | 1.5 | 0.8 | 129 |
| 5 | DBP (mmHg) | 80.3 | 12.2 | 148.8 | 5 | 76.3 | 1.5 | 0.8 | 109 |
| 6 | FBG(mmol/L) | 4.8 | 1.6 | 2.6 | 10 | 4.3 | 1.5 | 0.8 | 120 |
| 7 | WHR (none) | 0.82 | 0.2 | 0.0 | 5 | 0.779 | 1.5 | 0.8 | 278 |

***Source:*** (14)

2.5 Sampling procedures: This study will also apply a multistage cluster sampling whereby; three out of five districts have been selected randomly from Dar es Salaam region. Thereafter, mapping of market places (clusters) will be done and in each selected district two market places will be randomly selected then randomized one to receive an intervention package (health education and plate model) and another to receive a placebo (health education) . The step will be followed by mapping of food vendors to identify eligible food vendors and form a sampling frame per each cluster. Thereafter, probability proportion to size will be done to determine the number of vendors to be recruited per each cluster. Food vendors will be also selected randomly from each cluster to participate in the study. Each selected food vendor will identify regular customers then consent to participate in the trial will be sought from all identified clients (**Table 2**).

Table 2 Summary for sampling procedure

| **Stage** | **Ilala** | **Ubungo** | **Kinondoni** |
| --- | --- | --- | --- |
| 1. Identify the market places(MP)/clusters | 5 | 9 | 8 |
| 2. Identify and match eligible MPs | 5 | 9 | 8 |
| 3. Select randomly the required number of MPs for the study | 2 | 2 | 2 |
| 4. Assign MPs randomly into control and intervention arms | 2 | 2 | 2 |
| 5. Mapping Food vendors(FVs) | xx | Xx | Xx |
| 6. Identify eligible FVs | xx | Xx | Xx |
| 7. Use probability proportion to size (PPS) to allocate ≥50 FVs | xx | Xx | Xx |
| 8. Mapping of eligible* regular clients per FV | xx | Xx | Xx |
| 9. Seek consent and recruits all regular clients /FV | xx | Xx | Xx |

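### The sample size rests on normal quantiles and a flat design effect of 1.5 tied to no ICC or market size; with six randomised markets the implied 80% power falls to about 66% or less, even if 1.5 is accepted.

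*Protocol*

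**What the plan says.** Section 2.4 lists the ingredients of the calculation as "level of significance (Z_1-α_), power of the test (Z_1-β_), population standard deviation (δ) and population variance (δ^2", that is, normal quantiles with no numerical alpha, sidedness or power. The target is "reducing the mean of waist circumference by 5% after an intervention i.e. from 0.82 to µ_a_=0.78"; the figures are those of waist-hip ratio (WHR). Clustering and non-response are handled in one sentence: "A design effects (DE) of 1.5 to clear variance between clusters was applied and none response rate of 20" per cent. The governing row of Table 1 reads "7 | WHR (none) | 0.82 | 0.2 | 0.0 | 5 | 0.779 | 1.5 | 0.8 | 278". The same 1.5 and 0.8 are applied to all seven indicators. The 278 is taken as one arm: "This sample size will be doubled to include both arms (intervention and control". The executive summary gives the total: "A total of 556 consumers and at least 50 vendors of urban street cooked foods will be recruited".

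Section 2.1 fixes the number of clusters: "This study will be conducted in three already randomly selected districts and six market places (two per district"). Under section 2.5 one of the two markets in each district is randomised to the intervention and the other to control, so there are three markets per arm, paired by district. Neither an ICC nor a market size appears in section 2.4.

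**The concern.** A design effect is not a free constant. For clusters of average size m it equals 1 + (m−1)·ICC, so fixing it at 1.5 fixes the ICC once m is known. Here m is large, so 1.5 amounts to an assumption that markets hardly differ. That assumption is never written down, and it is applied equally to body size, lipids, glucose and blood pressure. Consumers reach the trial through shared vendors and must eat regularly from the same vendor, so similarity within a market needs to be argued rather than left implicit.

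The second issue is independent of the ICC. The design effect inflates the variance, but it does not allow for that variance being estimated from only six randomised units. Normal quantiles treat it as known.

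Specific objective 4 is the effectiveness test. If the real power is well below the implied 80%, a null result would say little, and readers of the protocol would not know it.

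**Working it through.** **Inputs.** From Table 1: WHR 0.82 to 0.779 (difference 0.041), SD 0.2, design effect (DE) 1.5, response factor 0.8. From sections 2.1, 2.4 and 2.5: 278 per arm, 556 in total, six markets, three per arm. One-sided alpha of 5% and 80% power are not stated. They are inferred because they reproduce Table 1.

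**1. Reproducing 278.** One-sample formula: n = [SD(z₀.₉₅ + z₀.₈₀)/Δ]² = [0.2 × (1.645 + 0.842)/0.041]² = 147.1, rounded up to 148. Then 148 × 1.5/0.8 = 277.5, so 278. The same formula returns the printed N for BMI, TC, TG, DBP and FBG. SBP gives 114 with the printed target of 122.2, and 129 only at about 122.6. Two-sided, 90%-power and two-sample variants do not return 278.

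**2. ICC implied by DE 1.5.** ICC = (DE − 1)/(m − 1).
- Recruited: m = 556/6 = 92.7, so ICC = 0.5/91.7 = 0.0055.
- Analysed: m = 0.8 × 92.7 = 74.1, so ICC = 0.5/73.1 = 0.0068.

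For assumed ICCs of 0.01, 0.02 and 0.05, DE is 1.92, 2.83 and 5.58 at 93 per market, and 1.73, 2.46 and 4.66 at 74.

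**3. Degrees of freedom.** Six markets less two arm means leave 4. With three district pairs, 3 − 1 = 2. One-sided 5% critical values: z 1.645, t(4) 2.13, t(2) 2.92. Two-sided: 1.96, 2.78, 4.30.

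**4. Changing only z to t, on the protocol's own standard error.** Analysed per arm: 278 × 0.8 = 222.4. SE = 0.2 × √(1.5/222.4) = 0.0164. Noncentrality = 0.041/0.0164 = 2.50. One-sided 5% power is 80% with z, 66% with t(4) and 50% with t(2), by the noncentral t distribution.

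**5. Two-arm standard error as well.** SE = 0.2 × √(2 × 1.5/222.4) = 0.0232. Noncentrality = 0.041/0.0232 = 1.77. With z, one-sided power is 55%; the fall from 80% to 55% is the one-sample formula alone. Few-cluster quantiles then give:

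| WHR power, unadjusted, 74 analysed per market | One-sided 5% | Two-sided 5% |
| --- | --- | --- |
| DE 1.5, 4 df | 43% | 28% |
| DE 1.5, 2 df | 33% | 18% |
| ICC 0.01 (assumed), 4 df | 39% | 25% |
| ICC 0.02 (assumed), 4 df | 31% | 19% |
| ICC 0.05 (assumed), 4 df | 21% | 12% |

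**6. Detectable difference.** On 4 df, 80% power needs a noncentrality of about 3.04 one-sided or 3.76 two-sided. At DE 1.5 this is 3.04 × 0.0232 = 0.071 (0.071/0.82 = 8.6%) one-sided, or 3.76 × 0.0232 = 0.087 (11%) two-sided. At an assumed ICC of 0.02 the two-sided figure is about 0.11 (14%). The target is 0.041 (5%).

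The 2 df figures use the same standard error as those on 4 df, so they credit the pairing with no gain. If the districts differ, pairing would shrink the standard error and recover part of the loss.

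**The case against.** Several stronger readings are tempting, and the documents do not support them.

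- *That an ICC of about 0.005 is wrong.* The protocol gives no ICC, so this value cannot be called false. What can be said is that 1.5 is unsupported and tied to no cluster size. The range 0.01 to 0.05 is an assumption.
- *That the 43% or 28% is all due to clustering.* It is not. The one-sample formula alone takes power from 80% to 55%; at DE 1.5 the degrees of freedom take it from 55% to 43%.
- *That no valid analysis could reach the target.* Baseline values are collected, and section 2.6.4 plans a mixed model for the pre-post analysis. If baseline adjustment removed 36% to 64% of the variance at both levels (an assumption), one-sided WHR power on 4 df at DE 1.5 would be about 57% to 78%. SBP (6.8 mmHg, two-arm standard error) is already at 73% one-sided without adjustment and would reach about 88% to 98%. Section 2.4 claims no such gain, so its calculation is not rescued, but the power figures above are for an unadjusted end-line contrast.
- *That more consumers in the same markets would barely help.* At ICC 0.0068, doubling them raises two-sided SBP power on 4 df from 55% to 71%. The statement becomes reasonable only at larger ICCs.
- *That vendor-level similarity needs its own inflation.* At 556/50 = 11.1 clients per vendor, an ICC of 0.05 gives DE 1 + 10.1 × 0.05 = 1.5. But the vendor is not the randomised unit. Similarity within vendors matters because it feeds the market ICC, and a market-level analysis absorbs it.

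None of this touches the core: no ICC behind 1.5, and normal quantiles for six randomised markets.

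**Conclusion.** The point stands in this form: the size in section 2.4 is wrong as written, because the design described does not deliver the power it implies. If 1.5 and the protocol's own standard error are accepted unchanged, power for WHR is about 66% on 4 df, or 50% on 2 df, instead of 80%. This needs no ICC assumption beyond the protocol's own. With the separate one-sample fault also corrected, it is about 43% one-sided or 28% two-sided on 4 df, and lower if the ICC is above 0.007.

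The conclusion rests on the inferred one-sided 5% and 80% inputs, equal market sizes, an end-line contrast without baseline adjustment, and an analysis that treats the market as the randomised unit. A reader might infer that the number of markets must be increased. The documents do not establish that. What is established is that the stated figures need correcting.

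**What to change.** In section 2.4:

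1. Replace the flat 1.5 with DE = 1 + (m−1)·ICC at the actual market size (93 recruited, 74 analysed), over a stated ICC range with its justification.
2. Use t quantiles with the degrees of freedom of the planned analysis: 2 if paired by district, at most 4 if not.
3. State alpha, sidedness and power, and any precision gain assumed from baseline adjustment.
4. Restate the power and detectable difference that 556 consumers in six markets deliver, using the two-arm standard error.

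This is a change of wording and figures, with no cost in participants or sites.

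Using more of the 22 markets in Table 2 ("1. Identify the market places(MP)/clusters | 5 | 9 | 8") is only an option to consider. Spreading the same consumers over 12 markets would raise two-sided SBP power from 55% on 4 df to about 75% with districts kept as strata (8 df, ICC 0.0068), but WHR only to about 40%. It would double the sites to map and visit each week, against a travel line of 500 euros in Table 6. If that is not affordable, the restated power should stand as the trial's declared limit.

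### Section 2.4 sizes a two-arm comparison with a one-sample formula: 278 per arm gives waist-hip ratio about 55% one-sided power (42% two-sided), not the built-in 80%, and falls short of Table 1's own N for triglycerides

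*Protocol*

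**What the plan says.** Protocol section 2.4 lists the ingredients of the calculation as "level of significance (Z_1-α_), power of the test (Z_1-β", with one standard deviation, a baseline mean and a target mean. WHR is the sizing indicator, with a target 5% below baseline, "i.e. from 0.82 to µ_a_=0.78". A design effect of 1.5 and 20% non-response are applied. The Table 1 row reads "WHR (none) | 0.82 | 0.2 | 0.0 | 5 | 0.779 | 1.5 | 0.8 | 278". Section 2.4 then says "This sample size will be doubled to include both arms (intervention and control", and the executive summary carries the total: "A total of 556 consumers and at least 50 vendors of urban street cooked foods will be recruited".

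Table 1 also has a row for triglycerides: "TG(mmol/L)* | 1.7 | 1.1 | 1.2 | 12 | 1.5 | 1.5 | 0.8 | 353". Section 2.6.4 names total, HDL and LDL cholesterol, triglycerides, body mass index, WHR and blood pressure as primary outcomes. It compares the arms at the end of the intervention by an independent t-test and adds a mixed model for the pre-post analysis.

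**The concern.** A baseline mean, a target mean and one standard deviation are the inputs for testing a single group against a fixed reference value. The trial does something else: it estimates a mean in each of two arms and tests the difference. That difference carries sampling error from both arms, so each arm needs twice the one-sample number. Doubling the total creates a second arm of the same size and nothing more.

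At stake is how the result will be read. If the planned WHR change is real, the unadjusted comparison would find it only about half the time. A null result could then be taken as evidence against the package when the trial was unlikely to detect its own target. Separately, Table 1 gives a larger size for one primary outcome than the size adopted, and section 2.4 does not comment on it.

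**Working it through.** **Inputs.** Means, standard deviations, design effect 1.5 and response factor 0.8 come from Table 1. The formula is a figure missing from the text at hand, so its form is recovered by reproducing the table. The WHR variance printed as 0.0 is 0.2² = 0.04 rounded. The WHR difference is 0.82 − 0.779 = 0.041.

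**Step 1: reproduce Table 1.** Take n = [SD(z₀.₉₅ + z₀.₈₀)/(µ₀ − µₐ)]² with (1.645 + 0.842)² ≈ 6.183. Round n up, multiply by 1.5/0.8 = 1.875, and round to the nearest whole number.

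| Row | n | × 1.875 | Printed N |
|---|---|---|---|
| BMI | 6.183 × 4.6²/1.1² → 109 | 204.4 | 204 |
| TC | 6.183 × 0.78²/0.2² → 95 | 178.1 | 178 |
| TG | 6.183 × 1.1²/0.2² → 188 | 352.5 | 353 |
| DBP | 6.183 × 12.2²/4.0² → 58 | 108.8 | 109 |
| FBG | 6.183 × 1.6²/0.5² → 64 | 120.0 | 120 |
| WHR | 6.183 × 0.2²/0.041² → 148 | 277.5 | 278 |
| SBP, printed means (6.8) | 6.183 × 21.3²/6.8² → 61 | 114.4 | 129 |

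Six of seven rows match exactly. SBP gives 129 only if the baseline is 122.2/0.95 = 128.6 before rounding: the difference is then 6.4, n is 69, and 69 × 1.875 = 129.4.

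Two-sample versions do not fit, since they give WHR values about twice the printed 278 or more. A one-sample two-sided version with the design effect alone gives 280 for WHR. It omits the stated non-response factor, misses the printed value, and is still one-sample.

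**Step 2: power of the planned comparison.** Effective n per arm = 278 × 0.8/1.5 = 148.3. The standard error of the difference is SD × √(2/148.3) = SD × 0.1161. For WHR this is 0.2 × 0.1161 = 0.0232, and 0.041/0.0232 = 1.765.

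- One-sided 5%: Φ(1.765 − 1.645) = 0.548.
- Two-sided 5%: Φ(1.765 − 1.960) = 0.423.

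The WHR difference detectable with 80% power is (1.645 + 0.842) × 0.0232 = 0.058 (0.058/0.82, about 7.0%) one-sided. Two-sided it is (1.960 + 0.842) × 0.0232 = 0.065 (about 7.9%).

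**Step 3: all rows at 278 per arm, two-sample, no baseline adjustment.**

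| Row | Difference | One-sided | Two-sided |
|---|---|---|---|
| TG | 0.2 | 47% | 35% |
| WHR | 0.041 | 55% | 42% |
| BMI | 1.1 | 66% | 54% |
| TC | 0.2 | 71% | 60% |
| SBP | 6.45 (5% of 129) to 6.8 (printed means) | 83–87% | 74–79% |
| FBG | 0.5 | 85% | 77% |
| DBP | 4.0 | 88% | 81% |

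**Step 4: triglycerides on the plan's own formula.** One-sample, 0.2/(1.1/√148.3) = 2.214 and Φ(2.214 − 1.645) = 0.715. The adopted 278 therefore misses 80% before the two-sample correction.

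**Step 5: what design effect 1.5 implies.** Clients per market are 556/6 ≈ 92.7, and from 1.5 = 1 + (92.7 − 1) × ICC the ICC is about 0.0055.

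**The case against.** **The formula is not visible.** True. Its form is inferred from the inputs, the Z₁₋α notation and six exact matches. A reader might add that alpha, power and sidedness are left unstated. The documents do not support that as a fault: the numerical values may stand in the missing figure, and the notation together with a directional hypothesis points to a one-sided test.

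**Not every outcome is underpowered.** This stands. A reader might infer that 278 per arm means 55% power for the trial as a whole. It does not: 55% belongs to WHR. SBP, FBG and DBP still reach 80% one-sided, though only DBP does two-sided.

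**Triglycerides may have been set aside deliberately.** That row carries an asterisk whose footnote is not in the text at hand, and section 2.4 names WHR as the sizing indicator. This may explain the choice. It does not change what 278 delivers for an outcome that section 2.6.4 calls primary.

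**The mixed model uses baseline data.** It could raise power. Taking the variance reduction as 1 − r² and keeping the design effect at 1.5, a baseline-endline correlation of about 0.70 (one-sided) or 0.78 (two-sided) would bring WHR back to 80%. Those correlations are assumptions; the protocol states none, and Table 1 reproduces without one.

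**Would doubling each arm repair it?** A reader might infer that the right size is simply twice 278 per arm. With six fixed markets it is not. At 556 per arm (about 185 clients per market) and ICC 0.0055, the design effect is 1 + 184.3 × 0.0055 ≈ 2.0 and effective n is 556 × 0.8/2.0 ≈ 222. One-sided WHR power is then Φ(0.041/(0.2 × √(2/222)) − 1.645) ≈ 70%.

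**Few clusters.** Six markets lower power further. A reader might attach a figure based on 4 degrees of freedom, but Table 2 matches markets and section 2.5 randomises one of two per district, so 4 ignores the pairing. The direction is clear; the amount depends on the cluster analysis chosen.

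**Conclusion.** The concern holds for the basis of the sample size. Table 1 uses a one-sample calculation, the trial makes a two-sample comparison, and doubling to 556 does not supply the missing factor of two in variance within each arm. For WHR, the outcome that set the size, power is about 55% one-sided or 42% two-sided against the built-in 80%. TG, BMI and TC also miss 80% on either sidedness under the unadjusted t-test. Independently of that, 278 is below the plan's own 353 for triglycerides.

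The power figures assume 278 recruited per arm, 20% loss, the Table 1 means and standard deviations, a 5% level, design effect 1.5 as given, and no baseline adjustment. Taking the text's rounded target of 0.78 (difference 0.04) instead of 0.779 would lower WHR power slightly, to Φ(0.04/0.0232 − 1.645) ≈ 53% one-sided.

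**What to change.** Keep 556 and change what is claimed for it.

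- In section 2.4, replace the formula with the two-sample one and state alpha, sidedness and power in words.
- Correct every row of Table 1, giving the power or detectable difference that 278 per arm delivers for each outcome. Show the SBP baseline unrounded, or recompute that row from the printed means.
- Say plainly that WHR, TG, BMI and TC do not reach 80% under the unadjusted t-test, and explain why 278 was adopted when the table gave 353 for TG.
- State the ICC behind design effect 1.5 (about 0.0055 at about 93 clients per market) and note that six paired markets reduce power further.
- If baseline adjustment is to be relied on, state the assumed baseline-endline correlation and give the adjusted power beside the unadjusted.
- Do not quote a larger per-arm requirement computed with the design effect held at 1.5, because it rises with clients per market.

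The cost is a rewrite of section 2.4 and Table 1. No extra participants are needed; the stated power becomes less favourable.
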